
### Pharmacokinetic interactions

Duloxetine is a substrate and inhibitor of CYP 2D6 [32] similar to MDMA [33]. Duloxetine may therefore increase MDMA plasma levels and vice versa. However, because MDMA itself inhibits CYP 2D6 (autoinhibition) the additive effect of duloxetine is expected to be small. Pretreatment with paroxetine which is considerably more potent in inhibiting CYP 2D6 than duloxetine increased MDMA plasma levels by only 30% [17]. Thus, we do not expect a relevant increase in MDMA Cmax or AUC when duloxetine is administered before MDMA (<30% increase in Cmax or AUC). On the other hand, MDMA may moderately increase Cmax and AUC of duloxetine thereby enhancing the pharmacodynamic interaction. This potential effect is not unwanted on the test day. However, we want to eliminate any carry-over effect from MDMA to the next test session to avoid elevated duloxetine levels due to MDMA-induced 2D6 inhibition. Therefore, test sessions will be separated by at least 10 days [33] to eliminate potential carry-over effects between sessions. The effect of CYP 2D6 inhibition on the PK of duloxetine has previously been studied and is moderate. Specifically, the maximum plasma concentration of duloxetine and the AUC increased 1.6-fold after pretreatment with the potent CYP 2D6 inhibitor paroxetine [32]. This moderate effect of 2D6 inhibition on the metabolism of duloxetine is explained by the fact that duloxetine is mainly metabolised by CYP 1A2 and only to a minor degree by CYP 2D6 [34].

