## Secondary Hypotheses

1. Duloxetine will reduce blood pressure and heart-rate increases produced by MDMA.
2. Duloxetine will increase Cmax and AUC0-6h of MDMA by <30%
3. MDMA will increase Cmax and AUC0-6h of duloxetine by <30%
4. MDMA and duloxetine will produce no severe adverse effects
5. Duloxetine will decrease neuroendocrine effects of MDMA

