## Schedule of experimental session

**Table 2** shows the schedule of events for each experimental session. Each of the four test sessions will last 10 h from 8:00 AM to 6:00 PM. Subjects will arrive at 8:00 AM at our CRC. Subjects will take duloxetine (120 mg) or placebo the night before the study session at 8:00 PM and another dose of duloxetine (120 mg) or placebo in the morning of the study day (8:00 AM). An indwelling intravenous catheter will be inserted into a subcutaneous vein of the forearm of the nondominant arm. MDMA (125 mg) or placebo is administered 4 h after duloxetine (12:00 AM). The acute effects of MDMA are expected to last for 4 h [42, 43]. Outcome measures (see below) will repeatedly be assessed during the study session. The sessions end at 6 PM. Subjects will be under continuous medical control until the effects of the drug have completely subsided (within 4-6 h after MDMA administration).

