### Blood sample collection (pharmacokinetics)

Blood samples (11x7.5 ml) will be collected on the study day -4, 0, 0.33, 0.67, 1, 1.5, 2, 2.5, 3, 4, and 6 h after MDMA or placebo administration. This will allow us to assess the pharmacokinetics of both MDMA and duloxetine and potential PK interactions of the two compounds. The design is optimized to assess effects of duloxetine on peak plasma levels of MDMA (time to Cmax = 2h) and AUC0-6h for MDMA [43]. Blood samples will be collected in heparinized tubes, centrifuged at 4C at 2000 rpm for 10 min, and the plasma is then stored at -20C (two aliquots) until analysis. Collection tubes labels will include the following information: study number, study day, subject number, and sample number. The date and actual blood sampling time will be recorded on the sample collection page in the CRF.

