## Study Drugs

### Duloxetine

Duloxetine (Cymbalta) is a potent and selective 5-HT and NE reuptake inhibitor [27]. Duloxetine (60 mg gelatine capsules) will be obtained from Eli Lilly (Suisse) SA, Vernier. The investigator pays for the product. Eli Lilly does not act as a sponsor for the study. The original company product will be used. However, capsules will be encapsuled with opaque dark-colored gelatine capsules and similar placebo capsules containing lactose will be prepared by a pharmacist. **Clinically used doses:** Duloxetine is used clinically in the treatment of depression, generalized anxiety disorder, diabetic and other neuropathy, and fibromyalgia. The clinically used common starting dose is 60 mg/day. Maintenance doses are 60-120 mg/day [25, 61, 62]. Several clinical trials have used 120 mg/day given once or in two doses of 60 mg twice per day. The suggested maximum dose is 120 mg daily. **Tolerability:** Duloxetine was well tolerated at doses of 60-120 mg/day [63]. See 14.1. for expected adverse effects of duloxetine. **Pharmakokinetics (dose finding and dosing intervals):** Elimination half-life of duloxetine is 12 h and Tmax is 6 h [61, 64]. On the test day, duloxetine (120 mg) will be given at 8 AM 4 h before MDMA administration at 12 AM so that the duloxetine Cmax will be reached shortly after the onset of the subjective MDMA effect (1h after MDMA administration) and together with Cmax of MDMA. An additional dose of duloxetine (120 mg) will be administered the day before MDMA at 8 PM, 16 h before MDMA administration. At both time-points duloxetine will be administered in a dose of 120 mg (maximum suggested therapeutic dose). Because the study uses only one dose of duloxetine it is important to use a relatively high dose to ensure effective plasma levels. Mean duloxetine plasma Cmax values were 22, 44, and 61 ng/mL after single oral doses of 30, 60, and 90 mg of duloxetine in healthy volunteers [64]. At steady state 40 mg once daily resulted in a mean Cmax level of 35 ng/mL and a trough level of approximately 10 ng/mL at 24h [32]. Population PK studies showed mean Cmax levels of 30-60 ng/mL follwing daily administration of 60 mg and depending on gender, smoking status, age and other variables [65]. Mean trough levels at 24h were in the range of 25 ng/mL. Women typically had 64% higher average steady-state concentrations than men (with considerable overlap). Similarly, nonsmokers had 43% higher average concentrations than smokers. Doubling the duloxetine dose from 30 mg to 60 mg and from 60 mg to 120 mg resulted in 2.3 fold and 2.6 fold higher average concentration values, respectively [65]. Based on these data we expect mean Cmax levels of 120-150 6 h after the administration of the second dose of 120 mg of duloxetine with the first dose (120 mg) given 12 h before the second dose. This Cmax is similar to the one seen in patients treated with daily doses of 120 mg under steady state conditions (peak 100 ng/mL, trough 50 ng/mL) [65]. **PD and PK interactions of duloxetine and MDMA** (see 7.2.1/2). **Relevant clinical studies using duloxetine in healthy volunteers**: Duloxetine (60 mg for 14 days) was not able to block the thyramine-induced increases in systolic blood pressure, indicating that the dose might be too low to block the NE transporter to a relevant extent in this test [66]. A dose of 80-120 mg was effective in suppressing the blood pressure increase due to thyramine [25]. However, there is clinical evidence that lower doses of duloxetine block NE transport. For example, urine catecholamine changes indicative of NE reuptake inhibition were present already at 80 mg. We suggest that a dose of 120 mg should be used for the present study. Of note, desipramine completely blocked thyramine-induced SBP responses which could indicate that desipramine interacts with stimulants at a different site on the NE transporter than duloxetine.

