## Analysis of outcomes

Repeated-measures analysis of variance (ANOVA) with drug (MDMA and duloxetine) as within-subject factors followed by Tukey’s post-hoc tests will be use to analyze differences between the different treatment conditions. Transformations will be performed before analysis, if response variables are nonnormally distributed. Pharmacokinetic parameters (Cmax, tmax, AUC from 0 to 6 h) will be obtained using *PK Functions for Excel*®. AUC values will be calculated by the trapezoidal rule. Additional PK analyses may be performed using *WinNonLin®* and *GraphPad®.* Statistical analyses will be performed using *Statistica*® *(StatSoft).*

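### The <30% bound on MDMA's effect on duloxetine Cmax and AUC0-6h says almost nothing about inhibited duloxetine metabolism, because duloxetine is given first and sampling stops 6 h after MDMA

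*Protocol*

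**What the plan says.** Section 8.2 of the protocol lists the effect of MDMA on duloxetine pharmacokinetics as a secondary endpoint. Section 9.2 attaches a number to it: "MDMA will increase Cmax and AUC0-6h of duloxetine by <30" per cent.

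The reasoning is in section 7.2.2. Both drugs are CYP2D6 substrates and inhibitors, and "MDMA may moderately increase Cmax and AUC of duloxetine thereby enhancing the pharmacodynamic interaction". The same section cites a 1.6-fold rise in duloxetine Cmax and AUC when paroxetine was given beforehand. It adds that CYP2D6 is a minor route for duloxetine and CYP1A2 the main one.

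The schedule is fixed elsewhere:
- Section 11.5.1: "An additional dose of duloxetine (120 mg) will be administered the day before MDMA at 8 PM, 16 h before MDMA administration".
- Section 11.3: "MDMA (125 mg) or placebo is administered 4 h after duloxetine".
- Section 11.5.1: "Elimination half-life of duloxetine is 12 h and Tmax is 6 h".
- Section 11.4.5 gives the sampling times (the first value carries a minus sign): "4, 0, 0.33, 0.67, 1, 1.5, 2, 2.5, 3, 4, and 6 h after MDMA or placebo administration". It says of this sampling: "This will allow us to assess the pharmacokinetics of both MDMA and duloxetine and potential PK interactions of the two compounds".
- Section 13.2 names the measures: "Pharmacokinetic parameters (Cmax, tmax, AUC from 0 to 6 h").

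**The concern.** The paroxetine benchmark comes from an inhibitor given before duloxetine. Here the order is reversed. When MDMA is swallowed, the first duloxetine dose is 16 h old and roughly three quarters of the second has been absorbed. MDMA can then act only on what is cleared, or still absorbed, during the next 6 h. The protocol does not mention that this order and window limit the effect that can appear.

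At stake is the reading of a secondary result. If the observed rise is below 30%, a report could say that MDMA has no relevant effect on duloxetine kinetics. That statement would rest mainly on dose timing. It would look much the same whether MDMA left duloxetine clearance alone or reduced it as much as a strong CYP2D6 inhibitor does.

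**Working it through.** **Inputs from the protocol.** Half-life 12 h and Tmax 6 h (11.5.1); doses at t = -16 h and t = -4 h, with MDMA at t = 0 (11.3, 11.5.1); samples at 0, 0.33, 0.67, 1, 1.5, 2, 2.5, 3, 4 and 6 h (11.4.5); benchmark 1.6-fold (7.2.2). AUC0-6h is taken as the 6 h after MDMA.

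**Model (assumed).** One compartment, first-order absorption, doses superposed, concentrations in units of one dose per volume.
- k = ln 2 / 12 = 0.0578/h.
- ka solves ln(ka/k)/(ka - k) = 6, giving ka = 0.365/h.
- Share of dose 2 unabsorbed at t = 0: exp(-0.365 × 4) = 0.232.

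**Check against the protocol's own figure.** Section 11.5.1 expects a Cmax of 120-150 (ng/mL) 6 h after the second dose. Scaling its single-dose values linearly to 120 mg gives 61 × 120/90 = 81 and 44 × 2 = 88 ng/mL. With f(t) = exp(-kt) - exp(-ka·t), the accumulation factor is 1 + f(18)/f(6) = 1 + 0.352/0.595 = 1.59. The prediction is 129-140 ng/mL (124-140 if an absorption lag of up to 3 h is assumed), inside the stated range. Linear scaling is an assumption, but the ratios below do not depend on the concentration level.

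**Without MDMA.** C(t) = [ka/(ka - k)] × Σ f(t - ti), with ka/(ka - k) = 1.188.
- C(0) = 1.188 × [(0.397 - 0.003) + (0.794 - 0.232)] = 1.135.
- Highest sampled value 1.142, at 0.67 h.
- C(6) = 0.969; AUC0-6h = 6.49.

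**Elimination fully stopped at t = 0.** The drug left to absorb is 0.232 + 0.003 = 0.235, so C(t) = 1.135 + 0.235 × (1 - exp(-ka·t)).
- C(6) = 1.135 + 0.235 × 0.888 = 1.344. Cmax ratio: 1.344/1.142 = 1.18.
- AUC0-6h = 1.135 × 6 + 0.235 × (6 - 0.888/0.365) = 7.65. Ratio: 7.65/6.49 = 1.18.

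**Clearance cut 1.6-fold at t = 0.** k' = 0.0578/1.6 = 0.0361/h.
- C(6) = 1.135 × 0.805 + [0.365 × 0.235/(0.365 - 0.0361)] × (0.805 - 0.112) = 1.095. Ratio at 6 h: 1.095/0.969 = 1.13.
- The same formula at the other sampling times gives a highest value of 1.173 (ratio 1.03) and an AUC of 6.89 (ratio 1.06).

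**Range.** Availability means the fraction of the not-yet-absorbed drug that reaches plasma. The protocol gives no value, so any change in it is an assumption.

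| Scenario from t = 0 | AUC0-6h | Cmax |
|---|---|---|
| Clearance ÷1.6 | +6% | +3% |
| Clearance ÷1.6, half-life 10-14 h | +7% to +5% | +3% to +2% |
| Clearance ÷1.6, availability ×1.6 | +13% | +10% |
| Elimination stopped | +18% | +18% |
| Stopped, availability ×1.6 | +26% | +29% |
| Stopped, availability ×2 | +31% | +36% |
| Stopped, half-life 10 h | +21% | +22% |
| Stopped, half-life 10 h, availability ×1.6 | +31% | +36% |

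The third row is generous: applied before dosing, the same two changes would multiply total AUC by 1.6 × 1.6 = 2.56, well above the 1.6-fold benchmark. Onset at t = 0 is generous too, since section 11.5.2.2 puts MDMA's own tmax at 120-144 min. With onset 1 h later, the first row becomes +4% and +1%.

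**How well the bound separates the cases.** Assume a within-subject CV of 30% and 16 subjects. The standard error of the log ratio is √ln(1.09) × √(2/16) = 0.104. The observed AUC ratio then stays below 1.3 with probability 99.4% if there is no effect and 97.5% if the true ratio is 1.06.

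**The case against.** The strongest reply is that <30% is a forecast, and a correct one. Section 7.2.2 already expects little change because CYP2D6 is a minor route. Section 11.4.5 says openly that sampling is optimised for MDMA. Section 13.2 attaches no test or decision rule to the bound, and sample size and early termination do not use it. What matters for the pharmacodynamic aim is duloxetine exposure during the MDMA session, which the 0-6 h comparison does measure.

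Much of this stands. Same-session exposure is a legitimate quantity, and the item is one of five secondary hypotheses. What does not follow is that meeting the bound supports the pharmacological reason for the forecast. The schedule would give the same result if that reason were wrong.

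A reader might infer more than the documents support:
- That hypothesis 3 cannot be false, or that the rise must stay under 20%. Stopped elimination with a half-life of 10 h gives +21% and +22%; total blockade combined with higher availability passes 30%; and a noisy estimate from 16 subjects could exceed 30% by chance.
- That the sentence "MDMA may moderately increase Cmax and AUC of duloxetine thereby enhancing the pharmacodynamic interaction" is an error. It is hedged, and a rise of 10-13% could fairly be called moderate.
- That the trial fails to answer how MDMA interacts with repeated duloxetine use. The protocol does not pose that question.

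**Conclusion.** The concern holds as a matter of interpretation. With the protocol's half-life and Tmax, inhibition at the paroxetine benchmark would move AUC0-6h by about 6% and Cmax by about 3%, or about 13% and 10% if availability of the unabsorbed dose also rose 1.6-fold. Stopped elimination would move each by about 18%. The <30% bound is therefore expected to be met with or without any plausible CYP2D6 inhibition, and it cannot tell the two apart. That is at odds with the statement in section 11.4.5 that the sampling allows interactions of both compounds to be assessed, as far as duloxetine metabolism is concerned.

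The conclusion rests on a one-compartment model, immediate and maximal inhibition at MDMA intake, and the protocol's kinetic values. It concerns the true mean effect, not every possible estimate. Crossing 30% needs combinations such as total blockade plus doubled availability, which do not fit the protocol's statement that CYP2D6 is a minor route.

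**What to change.** In sections 8.2 and 9.2, replace the <30% prediction for duloxetine with a descriptive item: the effect of MDMA on same-session duloxetine exposure, 0-6 h after MDMA, which is 4-10 h after the second duloxetine dose. Naming the window also removes doubt about the time origin; counted from the 8 AM duloxetine dose, even stopped elimination would move a 6 h AUC by only 2-3%.

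Report the duloxetine-MDMA to duloxetine-placebo ratios of AUC0-6h and Cmax with 95% confidence intervals. State that a ratio below 1.3 does not show absence of a metabolic interaction.

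If a more responsive exploratory measure is wanted, use the ratio of the 6 h concentrations, which rises about 13% under the 1.6-fold clearance scenario. The 3-6 h decline is no better than AUC0-6h: C(6)/C(3) goes from 0.884 to about 0.94, roughly 6%.

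Section 7.2.2 can stay as it is, and this point calls for no change to dosing or sampling. The cost is a few sentences and one summary from samples already drawn. The downside is giving up a secondary claim that the design cannot support.

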# STUDY DESIGN AND METHODS

## Study design

We will use a double-blind cross-over design with four treatment conditions. Treatment conditions are placebo-placebo, duloxetine-placebo, placebo-MDMA, and duloxetine-MDMA. Order will be balanced and pseudo-random. Each subject will participate in four 1-day study sessions with a washout period of two weeks (>10 days) between sessions. We previously used similar designs [18].

## Study duration

1.1.2010 to 31.12.2010

## Study site

Clinical Research Center, Division of Clinical Pharmacology and Toxicology, University Hospital of Basel, Switzerland,

## Study population

### Recruitment

Subjects will be recruited by word of mouth and by advertisements placed on advertising boards of university institutes of the University of Basel and on the homepage of the University. Similar to previous studies [18], we intend to include mainly healthy University students. Six-teen male or female subjects will be enrolled. Drop-outs will be replaced.

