# Data analysis

## Sample size estimation

Power analysis was performed with PASS®, Hintze J. Kaysville, Utah, US. We consider a relative reduction of 20% (MDMA vs. duloxetine+MDMA) in “good drug effects” to be clinically meaningful [13, 16, 17, 68]. A sample size of 13 achieves 82% power to detect a difference of 20 between the null hypothesis mean of 100 and the alternative hypothesis mean of 80 with a known standard deviation of 25 [13, 68] and with a significance level (alpha) of 0.05 using a two-sided one-sample t-test. For the most relevant secondary outcome, which is Psys, we expect that duloxetine will decrease the MDMA-induced increase in Psys by 10 mmHg from +30 mmHg (MDMA vs. placebo) to +20 mmHg MDMA+duloxetine vs. duloxetine). This effect of duloxetine would be relevant and similar to the one of citalopram on MDMA-induced increases in Psys [15]. A sample size of 8 achieves 81% power to detect a difference of 10 between the null hypothesis mean of +30 and the alternative hypothesis mean of +20 with a known standard deviation of the difference of 10 [15] and with a significance level (alpha) of 0.05 using a two-sided one-sample t-test. Assuming a drop-out rate before inclusion of 50% we will have to screen 32 subjects to include 16 in the study. Lower (8-12) [16, 17] or similar sample sizes [13, 47, 68, 82] were used in previous comparable studies. Subjects who prematurely discontinued the study for any reason will be replaced if the number of discontinued subjects exceeds three. A samples size of 8 or less is commonly used in PK studies. A larger sample is used here to produce meaningful results for the pharmacodynamic parameters.

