### Replacement policy

Subjects who withdraw from the study will be replaced if the number exceeds three subjects, to maintain at least 13 subjects. Replacement subject will follow the same treatment sequence as the withdrawn subject.

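### Section 10.4.1 replaces every drop-out, but sections 13.1 and 14.4.7 replace only after more than three; completers may number 13 to 16, and the floor of 13 rests on a power figure that the named t-test does not give

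*Protocol*

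**What the plan says.** Protocol section 10.4.1 (Recruitment) states "Six-teen male or female subjects will be enrolled", and the next sentence reads "Drop-outs will be replaced". No condition is attached.

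Section 13.1 (Sample size estimation) states "Subjects who prematurely discontinued the study for any reason will be replaced if the number of discontinued subjects exceeds three". Section 14.4.7 (Replacement policy) agrees with it and gives the reason: "Subjects who withdraw from the study will be replaced if the number exceeds three subjects, to maintain at least 13 subjects". It adds "Replacement subject will follow the same treatment sequence as the withdrawn subject".

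The floor of 13 comes from the primary power statement in section 13.1: "A sample size of 13 achieves 82% power to detect a difference of 20 between the null hypothesis mean of 100 and the alternative" mean of 80, "with a known standard deviation of 25", at a two-sided alpha of 0.05. The test named there is a one-sample t-test.

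Sections 10.1 (Study design) and 11.5.5 (Randomization and Blinding) describe the treatment order as balanced. Neither gives the number of sequences.

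**The concern.** If one, two or three enrolled subjects withdraw, section 10.4.1 requires them to be replaced, and sections 13.1 and 14.4.7 leave their places empty. Study staff cannot do both. Which section they follow decides how many subjects complete, how much power the primary comparison has, and whether the balanced order can be kept. The same-sequence rule in section 14.4.7 protects the order only for subjects who are actually replaced.

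The question is also more than editorial because the threshold of three is 16 minus 13, so the conditional rule is only as sound as the power claimed at 13. If that figure does not belong to the test the protocol names, the reason given for leaving three places empty is weakened.

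**Working it through.** **1. The rules side by side.** With 16 enrolled and w withdrawals:

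- Section 10.4.1: all w are replaced, which implies 16 completers.
- Sections 13.1 and 14.4.7: for w = 1, 2 or 3 nobody is replaced, so 15, 14 or 13 complete. Beyond three, replacement maintains at least 13.

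The rules differ for every w of one or more.

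**2. The stated power.** Inputs, all from section 13.1: difference 100 − 80 = 20, SD 25 taken as known, two-sided alpha 0.05, n = 13.

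Normal calculation with known SD: power = Φ(difference × √n / SD − 1.960). At n = 13 this is Φ(0.8 × 3.606 − 1.960) = Φ(0.924) = 0.822, which reproduces the stated 82%. The systolic pressure figure in the same section reproduces in the same way: n = 8, difference 10 and SD 10 give 0.807 against the stated 81%. Both figures are therefore known-SD normal calculations.

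**3. The test that is named.** For the two-sided one-sample t-test, power comes from the noncentral t distribution with n − 1 degrees of freedom and noncentrality 20 × √n / 25 = 0.8√n.

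| Completers | 0.8√n | Known-SD normal | Two-sided t-test |
|---|---|---|---|
| 13 | 2.884 | 82.2% | 75.4% |
| 14 | 2.993 | 84.9% | 79.0% |
| 15 | 3.098 | 87.3% | 82.1% |
| 16 | 3.200 | 89.3% | 84.8% |

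Going from 16 to 13 completers costs about 7 points on the normal calculation and about 9 points with the t-test. With the t-test, 15 is the smallest number that reaches 80%.

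**4. Balance of order.** There are four treatments and four periods, and each completer contributes one treatment to each period. For every treatment to appear equally often in a given period, it must appear n/4 times there. That is 4 at n = 16, but 3.25, 3.5 and 3.75 at n = 13, 14 and 15, which is impossible. This holds whatever sequences are used. Divisibility by four is necessary but not sufficient, so whether the order at 16 is in fact balanced depends on sequences that the protocol does not list.

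**The case against.** The strongest reply is that 13 is the number the protocol sized for. Section 13.1 claims 82% at 13, the figure reproduces on the stated known SD, and section 14.4.7 sets its floor accordingly. On those terms, three unreplaced withdrawals use up a margin and leave the target intact. This stands against one inference a reader might draw, that power is lost under the threshold rule. On the protocol's own calculation it falls from 89% to the planned 82%.

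A second reply is that the 75% comes from a separate defect, the mismatch between a known-SD calculation and a named t-test, which exists under either replacement rule. It is also not the power of the repeated-measures ANOVA with Tukey tests in section 13.2. Both statements are correct. The mismatch still bears on this point, because the floor is justified by the 82%. With the named test, full replacement keeps power above 80% and the floor of 13 does not.

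Third, section 13.1 uses the term drop-out for losses before inclusion, so the sentence in section 10.4.1 might concern those only. The wording permits this but does not favour it. The sentence directly follows the one on enrolment and has no such qualifier, and section 13.1 handles loss before inclusion by screening 32 subjects.

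Fourth, the two sections that agree are the ones that deal with the question in detail, and one of them gives a reason. Qualifying section 10.4.1 is therefore as legitimate a repair as extending its rule.

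**Conclusion.** The contradiction is real and lies in current text. Depending on the section followed, the trial ends with 13 to 16 completers. Primary power then ranges from 82.2% to 89.3% with known SD, or from 75.4% to 84.8% with the t-test that section 13.1 names. These figures rest on that section's difference of 20 and SD of 25, and they describe its one-sample comparison only. The floor of 13 is supported by the known-SD calculation and not by the named test.

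The effect on balance is partial. Up to three places stay empty, and exact balance by period is impossible at 13, 14 or 15. A reader might infer that balance is lost altogether, or that it means four subjects on each of four orders. The protocol does not state how many orders are used, so neither inference is supported. A reader might also suppose that withdrawals would cluster in sequences where an active session comes early. The protocol gives no rate or pattern of loss after inclusion, so this too is unsupported.

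The point should be settled before enrolment. It decides the final sample size and is cheap to correct.

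**What to change.** State one replacement rule in sections 10.4.1, 13.1 and 14.4.7. Either of two versions is sound.

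1. **Full replacement.** Replace each non-completer on the same sequence, as section 14.4.7 already provides, until 16 have completed, and remove the threshold of three from sections 13.1 and 14.4.7. Power with the named t-test is then 85%. Compared with the floor of 13, the cost is at most three more healthy volunteers (16 − 13).

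2. **Threshold rule.** Keep sections 13.1 and 14.4.7, qualify the sentence in section 10.4.1 to match, and restate the power at 13 as about 75% for the named t-test. Alternatively, raise the floor to 15, so that replacement starts once more than one subject has withdrawn (16 − 15 = 1). This gives 82% with the t-test and costs at most two more volunteers than the floor of 13. Either form should say that exact balance by period may not be reached. It should also say whose sequence the first replacement takes, since more than one subject will have withdrawn by then.

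Apart from any added volunteers, the cost is a wording change in the three sections.
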